## Methods

This study protocol is in accordance with the CONSORT guidelines concerning randomized controlled trials [26].

### Design and setting

A prospective, multicenter, three-armed, permuted block-randomized, double-blind, placebo-controlled, prophylactic intervention study will be conducted in critically ill patients with a high risk of delirium development. All participating sites are members of the Dutch Intensive Care Unit Delirium Consortium facilitating the collaboration related to delirium research in the ICU. In all centers, patients are screened for delirium using the validated Dutch translation of the Confusion Assessment Method-Intensive Care Unit (CAM-ICU) [27-29] by well-trained ICU nurses, at least two times a day and more often if indicated (during periods of fluctuating symptoms or levels of sedation). Before initiation of the study, ICU nurses will receive additional information concerning the CAM-ICU on top of their in-house CAM-ICU training. Furthermore, during the study, inter-rater reliability measurements of the CAM-ICU and the Richmond Agitation Sedation Score (RASS), as part of the CAM-ICU, will be performed in order to check the quality of the assessments, and if necessary, additional training will be provided.

The study will start after training of all centers including an initiation visit.

### Study population

#### **
*Inclusion criteria*
**

All consecutive critically ill patients admitted to the ICU aged ≥18 years at the time of ICU admission and with an expected length of ICU stay of over one day will be included as informed consent is obtained.

Data from patients that are included in the study, but who do not receive any study drug and are discharged from the ICU within 24 h will be discarded from further analysis. Patients who received at least one dose will remain in the study and patients in whom study medication had to be halved or stopped, e.g., because of prolonged QTc time or other side effects, will remain allocated to their study group and analyzed on an intention-to-treat basis.

#### **
*Exclusion criteria*
**

The following will be considered exclusion criteria: no informed consent obtained; history of epilepsy, Parkinson’s disease, hypokinetic rigid syndrome, dementia or alcohol withdrawal syndrome; patients admitted to the ICU for any other neurological disease (including post-cardio-pulmonary resuscitation patients, and patients admitted with coma due to overdose); patients treated with anti-psychotic therapy over the last 30 days prior to ICU admission; prolonged QTc-time (>500 msec) or history of clinically relevant ventricular arrhythmia in last 12 months; pregnancy/breast feeding; documented delirium prior to ICU admission; reasons that impair delirium assessment with the CAM-ICU (serious auditory or visual disorders, unable to understand Dutch or English; severely mentally disabled; serious receptive aphasia); ICU-stay less than one day; moribund and not expected to survive two days; known allergy to haloperidol.

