Given the fact that the development of delirium can be predicted only 24 h after ICU admission, and the clear relation between time to treatment with haloperidol and the duration of delirium [19], initiation of prophylaxis as early as possible is warranted. Based on our historical data, the median predicted risk of delirium is approximately 35% in patients with an expected stay on the ICU of over one day; this is considered a high risk for delirium development. A clinical estimation of an ICU LOS >1 day is possible within the first few hours after ICU admission. Previous studies that included patients using similar criterion of an expected ICU LOS were found feasible [20,21]. Therefore, the clinical estimation by the attending ICU-physician of an ICU LOS >1 day will be used as an inclusion criterion for this study, in which the prediction to develop delirium (using the PRE-DELIRIC model [18]) will be used to facilitate post-hoc analyses to investigate which patients benefit most from prophylactic therapy. By using the PRE-DELIRIC score as an *a priori* determined post-hoc analysis, we will learn if the putative beneficial effect of haloperidol is related to the risk to develop delirium, or comparable in all patients, independent of the baseline risk to develop delirium. In addition, it will facilitate the determination of a cut-off level for the PRE-DELIRIC score.

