### Objectives

Definitions of variables in objectives are reported in Table 1.

**Table 1 T1:** Definition of study objectives

**Objective**	**Definition**
*Survival days in 28 days*	Number of days that patients survive in 28 days. All patients will be classified as either ‘alive at study day 28’ or, if dead, ‘dead at study day 28’ on an intention-to-treat basis.
*Delirium diagnosis*	Patients are diagnosed as delirious when they have at least one positive CAM-ICU screening during their complete ICU stay. Patients who were not delirious during their ICU-stay are considered as non-delirious patients.
*Delirium-and-coma-free days in 28 days*	Number of days that the patient is alive and not delirious and not in coma over 28 days starting from the day of inclusion. A delirium-and-coma-free day is defined as a negative CAM-ICU screening with a Richmond Agitation Sedation Score (RASS) greater than (more alert than) -3/-4/-5 during a day. In case a delirious patient is discharged to the ward, a delirium-free day is defined as a delirium observation scale score [30] of less than 3 during a complete day.
*Duration of mechanical ventilation*	Time in days that the patient is on the mechanical ventilator. If the patient is ventilated mechanically several times during one ICU admission, then the ventilator times are added. Both invasive and non-invasive ventilation will be registered. Ventilator-free days (in 28 days) will be calculated.
*Incidence of re-intubation*	Patients who need to be intubated within 28 days from randomization, following a previous extubation, irrespective of the reason for re-intubation, are counted as incident case for re-intubation.
*Incidence of ICU readmission*	Patients who need to be readmitted to the ICU during within 28 days from randomization, irrespective of the reason for readmission, are counted as incident cases for ICU readmission.
*Side effects*	Drowsiness, agitation, QTc-time prolongation (using 12-leads ECG or monitor strip with Bazett’s formula) and development of extra pyramidal symptoms such as tandem gait, dystonia, tremor, myoclonus, tics, rigidity, akathisia [31], determined daily by physical examination by the intensivist.
*Serious adverse event*	Any untoward medical occurrence or effect at any dose that results in one of the following outcomes and is not classified as a clinical outcome of delirium or the underlying disease using the description above:

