### End of study medication

Prophylactic treatment with haloperidol will be continued until day 28, or discharge from the ICU (whatever comes first), or until delirium occurs. In the latter case, patients will be subsequently treated according to the delirium treatment protocol (with higher dosage of open label haloperidol).

In case delirium occurs, the patient’s study medication (prophylaxis treatment) will be stopped and the patient will be treated with open label haloperidol according to the delirium treatment protocol described below. Analysis will be on intention-to-treat basis. Study medication will not be restarted once delirium subsides, therapeutic haloperidol is stopped, or when a patient is re-admitted to the ICU within 28 days.

#### **
*Delirium treatment*
**

Patients with delirium (defined as a positive CAM-ICU test) will be treated with 2 mg haloperidol intravenously three times daily. Patients suffering from *hypoactive* delirium (only RASS scores between 0 and -3) and patients aged ≥80 years, weighing ≤50 kg, or with liver failure, will be treated with a lower dosage of 3x1 mg intravenously. Dosage can be increased up to a maximum of 3x5 mg in case of serious agitation or anxiety due to delirium. Additionally, midazolam, clonidine, propofol, or dexmedetomidine can be used as an escape therapy in case of serious agitation with insufficient efficacy of haloperidol according to usual patient care.

In patients treated for more than three days, the dosage will be halved when delirium subsides. When delirium does not reoccur the following day (CAM-ICU remains negative), the dosage will be halved again and then stopped the third day when the patient remains non-delirious. In case delirium occurs again during the reducing phase, the original dose will be restarted.

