### Ethics

The study will be conducted according to the principles of the Declaration of Helsinki (version 2008) and in accordance with the Medical Research Involving Human Subjects Act.

There are indications that early treatment of delirium is more effective than delayed treatment [37], but this needs to be confirmed in other studies. Since it is recognized that the onset of delirium occurs, on average, on day 2 after ICU admission, early preventive treatment is likely to be more effective. In the short-term, low dose haloperidol has no known relevant side effects, therefore randomization and administration of study medication will be started immediately following identification of a high-risk patient. When an informed consent procedure results in a delay of randomization, a deferred consent procedure may be followed. The informed consent procedure will be started as soon as possible, but always within 24 h following ICU admission. If no deferred informed consent can be obtained within 24 h, the patient will be excluded from the study and study drug administration will be stopped.

The medical ethical committee of Arnhem-Nijmegen (CMO) approved this study including this deferred consent procedure (CMO-number 2012/424). This trial is registered on clinicaltrials.gov: NCT01785290.

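### The delirium exclusion ends at ICU admission, not at randomisation, so a patient already CAM-ICU positive in the ICU can be enrolled and counted as a delirium outcome (minor)

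*Protocol article*

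**What the plan says.** All places are in the Protocol article.

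- **Study population, Exclusion criteria.** Two criteria carry an explicit time anchor at ICU admission: "documented delirium prior to ICU admission" and "patients treated with anti-psychotic therapy over the last 30 days prior to ICU admission". The only criterion that mentions the CAM-ICU concerns patients in whom it cannot be used.
- **Background.** On timing of eligibility: "A clinical estimation of an ICU LOS >1 day is possible within the first few hours after ICU admission".
- **Ethics.** "randomization and administration of study medication will be started immediately following identification of a high-risk patient". If consent would delay this, a deferred procedure may be used. The 24-hour limit applies to consent: "The informed consent procedure will be started as soon as possible, but always within 24 h following ICU admission". The same section says that "the onset of delirium occurs, on average, on day 2 after ICU admission".
- **End of study medication.** On how long study drug runs: "Prophylactic treatment with haloperidol will be continued until day 28, or discharge from the ICU (whatever comes first), or until delirium occurs". Open-label haloperidol then follows, whatever the allocated arm.
- **Objectives, Table 1.** "Patients are diagnosed as delirious when they have at least one positive CAM-ICU screening during their complete ICU stay".

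**The concern.** A prevention trial needs patients who are free of the condition when they are randomised. Here the delirium criterion checks this at ICU admission, and randomisation happens afterwards. No section requires the absence of a positive CAM-ICU at randomisation, and none caps the time from admission to randomisation.

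For a patient who screens positive in that interval and is then randomised, three things follow from the text:

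1. The patient meets no exclusion criterion.
2. The condition that ends study drug is already met, so there is no period in which prophylaxis can act. The delirium treatment is the same in all arms.
3. The positive screen lies within the ICU stay, so Table 1 counts it as a delirium outcome although it preceded treatment.

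Such patients add the same outcome to every arm. They pull delirium incidence and delirium-free days toward no difference and, to a lesser degree, 28-day survival. They also blur what the delirium endpoint measures, because it mixes prevalent with incident cases.

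The antipsychotic window has the same anchor. A dose given in the ICU before randomisation is not excluded, so some placebo patients may start with active drug on board.

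**Working it through.** **Reading the sections together**

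| Item | Time anchor in the article |
|---|---|
| Delirium exclusion | up to ICU admission |
| Antipsychotic exclusion | 30 days up to ICU admission |
| Randomisation and first dose | on identification of the patient, after admission; no upper limit |
| Delirium outcome | complete ICU stay |
| Re-intubation, ICU readmission | within 28 days from randomisation |

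The last row shows that the article anchors at randomisation where it chooses to. The interval between the first and third rows is covered by no exclusion, but it is covered by the delirium outcome. The rule that discards patients needs both no study drug and ICU discharge within 24 h, so it does not in general remove these patients.

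**The plan's own figure**

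Inputs (Sample size calculation and statistics): control median 18 days, hazard ratio 0.85, accrual 90 days, follow-up 28 days, power 0.80, two-sided alpha 0.05.

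- Events = 4 × (1.960 + 0.842)² / (ln 0.85)² = 1,189.
- Event probabilities (exponential survival, uniform accrual, hazard ratio in the direction written): 0.905 in control and 0.932 in intervention.
- Patients per group = 1,189 / (0.905 + 0.932) ≈ 647 to 648. The stated 647 is reproduced. The point contests no planned number.

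**Dilution of the survival contrast**

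Let f be the share of randomised patients already delirious. The documents do not give it, so it is varied. Assume no treatment effect in that share and equal mortality, so that f is also its share of events.

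- Diluted hazard ratio = exp((1 − f) × ln 0.85).
- Power = Φ((1 − f) × 2.802 − 1.960), at the planned 1,189 events.

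| f | Hazard ratio | Power |
|---|---|---|
| 0 | 0.850 | 0.80 |
| 2% | 0.853 | 0.784 |
| 5% | 0.857 | 0.759 |
| 10% | 0.864 | 0.713 |

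If mortality in that share were double (a further assumption), its event share would be 2f/(1 + f). At f = 10% this is 0.20/1.10 = 0.182, and the hazard ratio is about 0.875.

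**Dilution of delirium incidence (illustration)**

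Assume a control risk of 35% among patients free of delirium at randomisation (the median predicted risk in Background). Assume a risk ratio of 65/75 = 0.867 (the earlier historically controlled study). All already delirious patients count as cases in every arm.

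- Control risk = f + (1 − f) × 0.35.
- Intervention risk = f + (1 − f) × 0.35 × 0.867.

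| f | Control | Intervention | Risk ratio |
|---|---|---|---|
| 0 | 0.350 | 0.303 | 0.867 |
| 2% | 0.363 | 0.317 | 0.874 |
| 5% | 0.382 | 0.338 | 0.884 |
| 10% | 0.415 | 0.373 | 0.899 |

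**Plausibility of f**

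Against a 35% risk, f = 2%, 5% and 10% would mean that about 2/35 = 6%, 5/35 = 14% and 10/35 = 29% of all delirium had arisen before randomisation. With a gap of hours and mean onset on day 2, the lower end is the more plausible.

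**The case against.** The strongest reply is that the gap is short and the intent is clear. Randomisation follows identification at once, the length-of-stay estimate is possible within hours, and onset averages day 2. Delirium documented before admission is already excluded. The trial is called prophylactic, and study drug runs until delirium occurs, so starting it in a patient known to be delirious would contradict the treatment section.

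Most of this stands, and it limits the size. It does not remove the gap: an average onset on day 2 leaves room for cases on day 1, sites screen at least twice daily, and eligibility is judged against the listed criteria, not against the trial's name. Nor is this a detail that a condensed article leaves out. The article states the anchor, and the anchor is the wrong one.

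A reader might infer more than the documents support:

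- **That randomisation may routinely wait up to 24 h.** The 24-hour limit is on consent. With deferred consent, randomisation can come first.
- **That 5% to 10% of patients are affected.** No figure is given, and nothing in the text supports that share.
- **That earlier antipsychotic use removes the treatment contrast.** A non-delirious patient given an earlier dose still goes on to haloperidol or placebo. That is contamination, not a complete loss of effect. The abstract's remark that a lower dose is sometimes used as prophylaxis does not place such use in the trial ICUs before randomisation.
- **That the comparison is confounded.** Randomisation balances these patients on average, so the effect is dilution, without inflation of the type I error.

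**Conclusion.** The point holds as a minor one. As written, the delirium exclusion lets in a patient with a positive CAM-ICU recorded in the ICU before randomisation, and the delirium definition then counts that screen as an outcome. The consequence is dilution toward no difference, mainly in delirium incidence and delirium-free days and slightly in 28-day survival.

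The size rests on an assumed share of 2% to 10% with no treatment effect and equal mortality. The hazard ratio then moves from 0.85 to between 0.853 and 0.864, and in the illustration the delirium risk ratio moves from 0.867 to between 0.874 and 0.899. The true share is probably near or below the lower end. The power figures take the planned event count at face value; whether that count is realistic is a separate question.

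**What to change.** 1. End the delirium exclusion at randomisation: exclude patients with delirium documented before randomisation, including any positive CAM-ICU already recorded since ICU admission. Require no additional assessment and no delay. Patients not yet assessed, or not assessable at that moment, stay eligible.
2. In Table 1, count incident delirium only from CAM-ICU screens made after randomisation.
3. As a lesser point, let the 30-day antipsychotic window also end at randomisation, so that doses given in the ICU beforehand are covered.

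The cost is an amendment of two eligibility lines and one definition. It uses screening that is already routine, and the planned sample size does not change. A few patients become ineligible. Delirium that is present but not yet screened at an early randomisation will still be missed, which is the price of keeping the early start.

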### Objectives

Definitions of variables in objectives are reported in Table 1.

**Table 1 T1:** Definition of study objectives

**Objective**	**Definition**
*Survival days in 28 days*	Number of days that patients survive in 28 days. All patients will be classified as either ‘alive at study day 28’ or, if dead, ‘dead at study day 28’ on an intention-to-treat basis.
*Delirium diagnosis*	Patients are diagnosed as delirious when they have at least one positive CAM-ICU screening during their complete ICU stay. Patients who were not delirious during their ICU-stay are considered as non-delirious patients.
*Delirium-and-coma-free days in 28 days*	Number of days that the patient is alive and not delirious and not in coma over 28 days starting from the day of inclusion. A delirium-and-coma-free day is defined as a negative CAM-ICU screening with a Richmond Agitation Sedation Score (RASS) greater than (more alert than) -3/-4/-5 during a day. In case a delirious patient is discharged to the ward, a delirium-free day is defined as a delirium observation scale score [30] of less than 3 during a complete day.
*Duration of mechanical ventilation*	Time in days that the patient is on the mechanical ventilator. If the patient is ventilated mechanically several times during one ICU admission, then the ventilator times are added. Both invasive and non-invasive ventilation will be registered. Ventilator-free days (in 28 days) will be calculated.
*Incidence of re-intubation*	Patients who need to be intubated within 28 days from randomization, following a previous extubation, irrespective of the reason for re-intubation, are counted as incident case for re-intubation.
*Incidence of ICU readmission*	Patients who need to be readmitted to the ICU during within 28 days from randomization, irrespective of the reason for readmission, are counted as incident cases for ICU readmission.
*Side effects*	Drowsiness, agitation, QTc-time prolongation (using 12-leads ECG or monitor strip with Bazett’s formula) and development of extra pyramidal symptoms such as tandem gait, dystonia, tremor, myoclonus, tics, rigidity, akathisia [31], determined daily by physical examination by the intensivist.
*Serious adverse event*	Any untoward medical occurrence or effect at any dose that results in one of the following outcomes and is not classified as a clinical outcome of delirium or the underlying disease using the description above:
	- death that is not related to the underlying disease or sequel of the underlying disease, or death that is considered by the investigator to be related to study drug
	- prolonged inpatient hospitalization or re-hospitalization
	- a life-threatening experience (that is, immediate risk of dying)
	- persistent or significant disability/incapacity
	- congenital anomaly/birth defect
	- considered significant by the investigator for any other reason
*Sudden unexpected serious adverse reactions*	Unexpected adverse reactions are adverse reactions, of which the nature, or severity, is not consistent with the applicable product information. Adverse reactions are all untoward and unintended responses to an investigational product related to any dose administered.

#### **
*Primary objective*
**

To determine the effect of prophylactic haloperidol use on 28-days survival.

#### **
*Secondary objectives*
**

There are seven secondary objectives:

1. To determine the effect of prophylactic haloperidol use on 90-day survival; survival analysis stratifying for delirium incidence will be performed.

2. To determine the effect of prophylactic haloperidol use on the incidence of delirium.

3. To determine the effect of prophylactic haloperidol use on the number of delirium- and coma-free days in a period of 28 days.

4. To determine the effect of prophylactic haloperidol use on delirium related outcomes: time to successful extubation, incidence of re-intubation, incidence of ICU readmission, and incidence of unplanned removal of tubes and catheters.

5. To evaluate the incidence and severity of side effects of haloperidol prophylaxis.

6. To determine the effect of preventive haloperidol use on quality of life 1 and 6 months following ICU admission compared with a baseline measurement at ICU admission using the Short Form-12 (SF-12) questionnaire.

7. *A priori* defined post-hoc analyses:

a. To determine the preventive effectiveness of haloperidol in different patient groups based on the *a priori* risk to develop delirium: patients with a predicted risk up to 50%, 50–70%, 70–90%, above 90% will be evaluated.

a. To determine the preventive effectiveness of haloperidol in different patient groups: medical/surgical/trauma patients, per acute physiology and chronic health evaluation-II (APACHE-II) score (<20, 20–25, >25)

a. Effectiveness of prophylaxis when delirium is diagnosed based on 1, 2, or more days with positive CAM-ICU scoring.

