Potential side effects of haloperidol include extra pyramidal symptoms, drowsiness, agitation, and ventricular arrhythmias. The latter are extremely rare (only case-reports are published [22-25]) and dose dependent. With the haloperidol dosage that will be used in the present study (3x1 mg or 3x2 mg intravenously daily), no relevant side effects are expected, regardless of underlying condition, organ dysfunction, and concomitant medication. Nevertheless, and given the preventive nature of this study, extra attention is being paid to the recognition of possible side effects of haloperidol that could mitigate its potential beneficial effects. Importantly, in three recent prophylactic haloperidol studies [11,17,19] no relevant side effects, and in particular no ventricular arrhythmias, were reported using similar low dosages of haloperidol as described in the present protocol. Regarding the choice of haloperidol dosage, this was based on the previous study in which no relevant side effects were found when using a prophylactic dose of 3x1 mg in delirium high-risk ICU patients, and resulted in a significant decrease of delirium incidence [19]. However, in this high-risk group (mean delirium risk of 75%) the incidence was still 65%, suggesting that a higher dosage of haloperidol might decrease the incidence of delirium to a greater extent. For this reason, and taking into account the non-relevant side effects, we choose to add a third arm using a higher dose of 3x2 mg haloperidol.

The aim of this study is firstly to determine the effect of two different low dosages of prophylactic haloperidol on 28-day mortality as well as the incidence of delirium and other delirium related outcome measures and quality of life, compared with placebo, in ICU patients with an expected ICU stay of >1 day. Secondly, to relate the potential beneficial effects of haloperidol to the *a priori* risk of developing delirium, using the PRE-DELIRIC model [18]. Lastly, to evaluate possible side effects of prophylactic haloperidol.

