**Figure 1 F1:**
[figure not shown]
CONSORT flowchart of patient enrollment.

A safety, futility, and superiority interim analysis will be performed by the DSMB after 175, 350, 500 (safety and futility) and 1,000 (safety and superiority) patients are included. Differences in serious adverse events between intervention and placebo are used for safety analyses and the primary endpoint 28-day survival is used to determine futility or superiority of intervention or placebo.

After the inclusion of 1,000 patients, superiority will be tested. A proven superiority (*P < 0.003, two-sided)* of any dose of haloperidol over placebo or a proven superiority (*P < 0.003, two-sided)* of placebo over haloperidol determined during the interim analysis will result in an alpha of 0.049 (two-sided) for the final analysis. This alpha distribution was calculated by an independent statistician according to the method of Lan-DeMets cumulative alpha spending function of O’Brien-Fleming alpha spending [36].

Data will be analyzed according to the intention-to-treat principle. For the descriptive statistics, continuous variables will be given as mean with standard deviation or median and inter quartile ranges, depending on their distribution. Normally distributed variables will be tested using Student’s *t*-test for comparison and Mann-Whitney U-tests for non-normally distributed variables. Categorical (and binary) variables will be presented as numbers and percentages and will be analyzed using the χ^2^ test. Survival analyses with Kaplan-Meier curves will be used as graphical representation. Cox proportional hazard regression analyses will be used to estimate the hazard ratio for survival with the use of haloperidol versus placebo. Furthermore, we will perform adjusted analyses for relevant covariates (including delirium, APACHE-II score, age, sex, sepsis, and other differences between the three study groups irrespective of the possible imbalance between the three groups). For this covariate analysis, univariate logistic regression analysis will be performed first in order to test the strength of the relationship. Subsequently, variables significantly associated with the dependent variable will be included in the covariate analyses.

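### Delirium incidence classes patients who die first or are never assessable as non-delirious, so the comparison is biased if either differs by arm; its window also has no stated start at randomisation

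*Protocol article*

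**What the plan says.** The second secondary objective is "To determine the effect of prophylactic haloperidol use on the incidence of delirium". Table 1 (Objectives) defines the case: "Patients are diagnosed as delirious when they have at least one positive CAM-ICU screening during their complete ICU stay". It then places everyone else: "Patients who were not delirious during their ICU-stay are considered as non-delirious patients". No exception is made for death before a positive screen, or for a patient who never had a valid CAM-ICU.

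The section on sample size and statistics covers binary variables in general terms, "Categorical (and binary) variables will be presented as numbers and percentages", with a chi-square test. It does not name delirium incidence, but no other analysis of that endpoint is given.

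Other rows of Table 1 are built differently. Delirium-and-coma-free days are the "Number of days that the patient is alive and not delirious and not in coma over 28 days starting from the day of inclusion". Re-intubation and ICU readmission are counted within 28 days of randomisation. The only delirium-related exclusion in the study population section is "documented delirium prior to ICU admission".

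**The concern.** The endpoint is meant to show prevention, yet two outcomes that are not prevention are scored as success: death before any positive screen, and coma or sedation too deep for the CAM-ICU throughout the stay. Both could differ by arm. Mortality is the primary endpoint. The Background states: "Potential side effects of haloperidol include extra pyramidal symptoms, drowsiness, agitation"; and sedation effects are among the side effects monitored. An arm with more such patients would show lower incidence even if the drug prevented nothing.

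The same classification is used in two further places: the 90-day survival analysis stratified by delirium incidence, and the covariate-adjusted analyses that include delirium. In both, patients who died early without a positive screen sit in the non-delirious group.

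The second issue is the window. The phrase "at least one positive CAM-ICU screening during their complete ICU stay" sets no start at randomisation. Read literally, a positive screen between ICU admission and randomisation is counted as a failure of a drug not yet given.

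**Working it through.** **Inputs from the article.** Median predicted delirium risk about 35% (Background). Anticipated placebo mortality 12% (Abstract). Earlier delirium incidence 65% against 75%, risk ratio 65/75 = 0.867 (Background). 647 patients per group before dropout (sample size section).

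**Plan's own figure.** No sample size or power is given for delirium incidence, so there is none to reproduce for this endpoint. The 647 belongs to the survival comparison and serves here only as an arm size. It does reproduce: 1,189 events for a hazard ratio of 0.85, divided by the mean event probability (0.905 + 0.932)/2 and by 2 arms, gives 647.

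**Assumed input.** The share *u* never assessable or dead before any positive screen. The documents give no value, so a range is shown.

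**1. Size of the bias with no drug effect.** Observed incidence = 0.35 × (1 − *u*). Rejection rates are for a nominal 5% two-proportion test at 647 per arm (normal approximation).

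| *u* placebo | *u* haloperidol | Incidence placebo | Incidence haloperidol | Spurious reduction | Rejection rate |
|---|---|---|---|---|---|
| 5% | 8% | 33.25% | 32.2% | 1.05 points | 6.9% |
| 5% | 10% | 33.25% | 31.5% | 1.75 points | 10.3% |
| 10% | 10% | 31.5% | 31.5% | 0 | 5.0% |
| 10% | 12% | 31.5% | 30.8% | 0.7 points | 5.9% |
| 10% | 15% | 31.5% | 29.75% | 1.75 points | 10.5% |
| 10% | 20% | 31.5% | 28.0% | 3.5 points | 28.0% |

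In the last row the rejection rate runs from 23.6% to 44.4% as delirium risk in assessable patients goes from 30% to 50%. For scale, a risk ratio of 0.867 at 35% is a true effect of 0.35 × (1 − 0.867) = 4.7 points, so 1.05 to 1.75 points is about 22 to 37% of it.

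**2. Death part alone.** Mortality in the haloperidol arm = 1 − 0.88^HR.
- HR 1/0.85 (harm): 13.96%, an excess of 1.96 points. If every extra death came before any delirium, the shift is 0.35 × 1.96 = 0.7 points in favour of haloperidol.
- HR 0.85 (benefit): 10.3%, a deficit of 1.7 points. The shift is at most 0.35 × 1.7 = 0.6 points against haloperidol.

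**3. Positive screens before randomisation.** Let a share *f* of placebo-arm cases (assumed) fall before treatment, equal in number in both arms. Observed risk ratio = *f* + (1 − *f*) × 0.867.

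| *f* | Risk ratio | Power at 647 per arm, 35% incidence |
|---|---|---|
| 0% | 0.867 | 43% |
| 10% | 0.880 | 36% |
| 20% | 0.893 | 30% |
| 30% | 0.907 | 24% |

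This bias is toward no difference.

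**4. What an alternative analysis shows.** Take 5% against 10% from step 1.
- Cumulative incidence with death as a competing event, under complete follow-up, ends at the crude proportions, 33.25% and 31.5%. Gray's test compares those same curves, so neither removes the bias.
- With an assessable-only denominator, incidence is 35% in both arms.
- With death and never-assessable counted as failures, the figures are 33.25 + 5 = 38.25% and 31.5 + 10 = 41.5%. The direction reverses, which shows that the crude result depends on the classification.

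**The case against.** The strongest reply has four parts.

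- **Coma is not drowsiness.** To be never assessable, a patient must stay deeply sedated for the whole ICU stay. Screening is at least twice daily, one positive suffices, and the Background expects no relevant side effects at these doses. This stands: a large imbalance is not shown to be likely.
- **Early death is limited.** Patients expected to die within two days are excluded, and under the trial's own hypothesis the death part works against haloperidol. This also stands.
- **The start of counting is open to reading.** The phrase about the ICU stay may only mean that screening runs to ICU discharge. Study drug is meant to start promptly, and delirium onset is put at day 2 on average. So the share before randomisation may be small. The text still fixes no start, whereas neighbouring rows do.
- **Other endpoints cover much of this, and detail belongs in an analysis plan.** Delirium-and-coma-free days do require the patient to be alive and out of coma, and are a partial cross-check. But the default to non-delirious is a printed rule, not an omission left to a later document.

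A reader might infer that the ICU-stay window also makes sedation or early death look like prevention. It cannot: randomisation balances cases that arise before it, and they only dilute.

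**Conclusion.** The classification rule is a real weakness of a secondary endpoint. It biases the incidence comparison only if never-assessable patients, or deaths without delirium, differ by arm. At 35% delirium the bias is 0.35 points for each point of imbalance: about 1 to 2 points for an assumed 3 to 5 point excess, with the false-positive rate rising from 5% to about 7 to 10%. The death part is at most about 0.7 points at 12% placebo mortality. A reader might go further and conclude that any observed reduction would be an artefact of sedation or death. The documents do not support that: they give no never-assessable rate, and the mechanism needs a sizeable imbalance to mislead on its own.

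The window is a separate and milder fault, resting on a literal reading. It costs power and pulls the risk ratio toward 1. The primary endpoint as defined, 28-day survival, is unaffected.

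**What to change.** - Count incident delirium from randomisation, as the re-intubation and readmission rows already do. Handle patients with a positive CAM-ICU before randomisation separately. Starting at first dose instead would bring in an exclusion made after randomisation.
- Report four categories by arm: delirious; assessable and never delirious; never assessable; died without delirium. State in advance where a patient who was never assessable and then died belongs.
- Add a cause-specific hazard analysis, censoring at death and at ICU discharge without delirium. This deals with death; persistent coma is dealt with by the categories and the next item.
- Add a sensitivity analysis on delirium or death, with never-assessable patients also counted as failures.
- Do not rely on Gray's test or cumulative incidence alone.
- Interpret incidence beside delirium-and-coma-free days.

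The cost is wording and slightly more analysis work. CAM-ICU, RASS and survival data are already needed for other endpoints.
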